### 2.5. Procedure

#### 2.5.1. Intervention

##### Digital Health Services Group (DHSG)

Children randomized to the DHSG will engage in a home-based hybrid (synchronous and asynchronous), remotely administered exercise program and ACTs for 12 weeks. The prescribed weekly regimen will consist of 50 min remote sessions: two synchronous, supervised sessions conducted via the Vsee platform, and a minimum of one asynchronous, unsupervised session. Children will be encouraged to maintain daily adherence to the exercise protocol.

Secure access to the VSee platform will be granted through a unique identification code assigned to each child. Parents/guardians will receive written and verbal instructions regarding the Vsee platform setup, the equipment’s proper use, and safety procedures, including “actions in an emergency” in case of adverse events or technical issues. Adverse events are defined as unintended injuries or clinical incidents resulting from study participation. These include complications such as paroxysmal cough, severe dyspnea, oxygen desaturation (4% drop in SpO_2_), musculoskeletal injury, or loss of balance. To ensure safety in any adverse event (e.g., falls, injury, etc.), at least one parent or guardian will be required to be present in person with the child during sessions. Additionally, written first-aid advice will be given. All adverse events will be recorded during the synchronous videoconferencing sessions. The physiotherapist will document the nature, severity, and duration of each event in a standardized log.

Children will perform ACTs (including individualized teaching and review of postural drainage, percussion, vibration, ACT devices, huffing, coughing), diaphragmatic breathing, and blowing games to enhance mucus expectoration. Both children and parents will be taught how to perform these techniques. During the synchronous, supervised videoconference sessions, the DHSG will be monitored/supervised by the pediatric respiratory physiotherapist for the proper performance of ACTs (device or non-device). All children will perform ACTs once a day for ten minutes. In case of mucus excess, they will be suggested to increase the performance to twice a day. ACTs will be chosen based on children’s ability to use/cooperate and preferences.

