Building upon a previous study in children with CF [11], our research team designed an exercise program based on the 24-letter Greek alphabet, where each letter represents an individual aerobic or strengthening exercise, selected so that they can be implemented easily in an online setting at home with minimal equipment. For example, the Greek letter “A” represents the exercise “ALMA”, meaning jumping up and down. In order to adapt the exercise program to age-specific needs and capabilities, the exercises have been modified for two age groups: 6–9 and 10–12 years old. The exercise program consists of 16 exercises per session, varied on the four-letter words chosen at a time. At each session, a combination of four words will be performed and modified weekly. All children will follow the same word combination every week. The exercise program will last 25 to 30 min per session.

The exercise workload will be equal to 60–75% of the maximum heart rate (HR) [20]. The target heart rate (THR) will be calculated based on the following Karvonen formula [21]:THR = [(HR_max_ − HR_rest_) × % intensity] + HR_rest_

Exercise parameters (heart rate, oxygen saturation) will be measured before and at the end of the exercise program by the parents/guardians attending the session. Dyspnea and leg fatigue will be evaluated using the Dalhousie Pictorial Scale [22]. The exercise program will be delivered and monitored by a pediatric respiratory physiotherapist.

Additionally, children and their parents/caregivers will be granted access to a website (www.fysao.gr) for disease management, including information about common symptoms, nutrition, pharmacological treatment, exercise, and ACT performance. The DHSG will utilize this specifically designed digital interface, the development and structural framework of which have been previously detailed by our research team [17]. To facilitate adherence and longitudinal monitoring, the DHSG will receive automated weekly reminders for ACTs and exercise performance. Through the web portal’s integrated evaluation forms, children can report daily symptomatology and track any clinical fluctuations. All the ACTs and the exercises have been digitized as high-definition videos and images, ensuring asynchronous accessibility for the DHSG. Furthermore, the platform facilitates secure communication, enabling children and their parents/caregivers to communicate with healthcare professionals via integrated email or direct document transmission.

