### 2.6. Remotely Administered Educational Session

The DHSG will receive a remote synchronous session of 1 h with guidance regarding familiarization with the use of the VSee platform. The Vsee platform is a secure, high-resolution videoconferencing software. It is easy to use, and it does not need to download any software system to the device. During this session, a verbal presentation will be carried out on how children and parents have to use the equipment to measure their heart rate, oxygen saturation, and how they should assess dyspnea and leg fatigue with the Dalhousie Pictorial Scale. Furthermore, parents/guardians will be trained on the proper use of the above equipment. Additionally, verbal instructions will be given to minimize difficulties relating to internet connection.

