##### Compliance with the Airway Clearance Techniques and Exercise Program

Compliance with the ACTs will be recorded using a detailed diary that includes weekly symptoms, type, frequency, and duration of ACTs performed. For both groups, compliance will be assessed twice a month, following the completion of this diary. The DHSG will complete the diary through the website, while the CG will complete it in a paper version via a phone call from a physiotherapist. Furthermore, the DHSG’s exercise program compliance will be assessed every second online session through a Microsoft Form diary. Documentation of the percentage of completed synchronous videoconferencing sessions will also be performed.

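### No home heart-rate or SpO2 reading is scheduled during the 25–30 min exercise block; one mid-block reading would be a cheap improvement (low severity)

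*Protocol article*

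**What the plan says.** All of this is in the Protocol article, mostly under Digital Health Services Group (DHSG) in section 2.5.1.

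- **Timing of readings.** Heart rate and oxygen saturation "will be measured before and at the end of the exercise program by the parents/guardians attending the session". The exercise block is 25 to 30 min long.
- **Structure of the block.** "At each session, a combination of four words will be performed and modified weekly". Each session has 16 exercises.
- **Intensity.** The workload is set as a heart-rate target of 60–75%. "The exercise program will be delivered and monitored by a pediatric respiratory physiotherapist". The Discussion (section 3) bases the primary hypothesis partly on live supervision keeping intensity where it should be.
- **Adverse events.** The listed complications include "oxygen desaturation (4% drop in SpO_2"), with no minimum duration. "All adverse events will be recorded during the synchronous videoconferencing sessions", and the physiotherapist logs the nature, severity and duration of each.
- **Sessions.** Each week has two supervised video sessions and "a minimum of one asynchronous, unsupervised session", for 12 weeks.
- **Equipment and training.** Section 2.6 teaches families "how children and parents have to use the equipment to measure their heart rate, oxygen saturation".
- **Compliance tracking.** Section 2.8.1 uses a diary for the exercise program, and "Documentation of the percentage of completed synchronous videoconferencing sessions will also be performed". Heart rate is not named there.

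**The concern.** The protocol defines one adverse event by a pulse-oximeter value and prescribes exercise by a heart-rate value, yet it schedules neither measurement while the child is exercising. A fall or a coughing fit can be seen on video. A symptomless fall in saturation can be found only by a reading.

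Two modest things are at stake. The first is the completeness of the adverse-event log for silent drops that resolve before the end. If a drop is found at the end, its onset and lowest value are also unknown, although the log asks for severity and duration. The second is whether the physiotherapist has a number in time to raise or lower effort within the same session. All children follow the same weekly word combination, varied only by two age bands, so individual heart-rate responses may well differ.

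**Working it through.** The plan gives no figure on this point to reproduce. The check is a count of scheduled readings, followed by an illustration that rests on stated assumptions.

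**Counts (inputs from section 2.5.1; 16 children per group from section 2.9)**

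- Supervised sessions: 2 × 12 = 24 per child; 24 × 16 = 384 in the arm.
- Unsupervised sessions, minimum: 1 × 12 = 12 per child.
- Share of prescribed sessions with live reporting: 24 / (24 + 12) = 0.67 at most.
- Scheduled readings inside the block now: 0. Longest gap: 25–30 min.
- With one mid-block reading in each supervised session: 24 per child, 384 in all. Longest gap: 25/2 = 12.5 to 30/2 = 15 min, if the four words take equal time (assumption).

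**Illustration: chance that a reading meets a silent drop**

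Let T be the block length and d the length of the drop, with d below T/2 and readings treated as instantaneous. The drop lengths and onset patterns are assumptions; the article gives neither.

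| Onset of drop | End reading only | Mid-block + end | d = 1, T = 30 | d = 5, T = 25 |
|---|---|---|---|---|
| Uniform over the block | d/T | 2d/T | 3.3% → 6.7% | 20% → 40% |
| First half only | 0 | d/(T/2) | 0% → 6.7% | 0% → 40% |
| Second half only | d/(T/2) | d/(T/2) | 6.7% → 6.7% | 40% → 40% |

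One mid-block reading therefore doubles the chance under uniform onset, makes early drops detectable, and adds nothing for drops that start after it. These are chances per drop. Without a desaturation rate they cannot be turned into a number of missed events, and that number could be zero.

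The heart-rate gain needs none of these assumptions: it is one in-exercise value per supervised session, where none is scheduled now.

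**Cost in time.** At an assumed 20–60 s for the reading, the pause takes 20/1,800 = 1.1% to 60/1,500 = 4% of the block.

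**Cost in artefact.** Assume a false low value in p = 1–5% of readings.

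- End reading alone, unrepeated: 1–5% of sessions, or 384 × 0.01 = 4 to 384 × 0.05 = 19 sessions.
- Two readings, unrepeated: 1 − 0.99² = 2.0% to 1 − 0.95² = 9.8%, or 8 to 37 sessions.
- Two readings, each low value repeated once, with independent errors: 1 − (1 − 0.0001)² = 0.02% to 1 − (1 − 0.0025)² = 0.5%, or at most about 2 sessions.

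If the cause of the artefact persists (a cold or moving hand), the repeat helps less.

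**The case against.** The strongest reply is that this is a preference for more readings, not an error. The article does not say that readings are taken *only* at those two times, ad hoc readings are not excluded, and a condensed article may leave the mechanics of monitoring to a fuller document. That is fair as far as it goes. It rules out a reader's inference that the protocol contradicts itself or forbids readings during exercise. It does not remove the point, because the article does state a schedule and that schedule has no in-exercise reading.

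Several safeguards also stand. A parent is in the room, the physiotherapist watches on video, dyspnea and leg fatigue are rated on the Dalhousie scale, and children must be clinically stable at entry. Cardiorespiratory parameters are recorded during the baseline clinic tests (sections 2.8.1 and 2.8.2), although the article does not name SpO2 there or give an action threshold. Symptomatic drops should therefore be noticed, and the gap narrows to silent drops that recover before the end. One can also question whether a symptomless dip is the kind of clinical incident the definition has in mind, although the 4% criterion carries no symptom requirement.

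A reader might infer that intensity goes unchecked. The documents do not support that: the end heart rate can be compared with the target and used to adjust the next session. What it cannot do is guide the session in which it is taken.

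Finally, a reading at every break between words would cost three pauses, up to 3/25 = 12% of the block at 60 s each, with more artefact and more interference with the intervention under test. That objection succeeds against so dense a schedule. It has much less force against a single pause.

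**Conclusion.** The point holds as a low-severity improvement to a stated schedule. No home reading is scheduled for 25–30 min of exercise. As a result, a silent 4% drop that recovers before the end can go unrecorded, and no scheduled heart-rate value arrives in time to adjust effort in that session.

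The counts (0 readings now, 24 per child with the change) follow from the text. The detection percentages are illustration only and range from a clear gain to none, depending on when drops are assumed to start.

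A reader might go on to infer that adverse events will be materially under-counted or that the trial's result is at risk. Neither follows. The article gives no desaturation rate, and no safety or intensity endpoint is built on these readings. The modified shuttle walk comparison, the sample size, the power and the analysis do not use them.

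**What to change.** Keep the before and end readings, and make these changes to section 2.5.1:

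1. Add at least one scheduled parent reading of heart rate and SpO2 near mid-block, for example straight after the second of the four words.
2. In supervised sessions, have the parent report it to the physiotherapist so that effort can be adjusted to the target.
3. Judge the 4% drop against the pre-session value, and repeat a low reading once before calling it an event.
4. Log the lowest SpO2 and the highest heart rate for the session.

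The device, the parent's presence and the parent's training are already planned. The cost is one pause of under about a minute per session, two log fields and some additional artefactual readings. The mid-block value is taken in a pause, so it should be read at once. Drops between readings can still be missed, and unsupervised sessions still have no live check.

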##### Control Group (CG)

Participants in the control group will receive the usual care, typically comprising inhaled antibiotics and/or bronchodilators for respiratory infections as regular pharmacological treatment in clinically stable condition and a 40 min, in-person, physiotherapy session where they will be taught ACTs to perform at home. A printed copy of a handbook, including information on their disease and symptoms, nutrition, pharmacological treatment, exercise, and how to perform ACTs, will be provided.

### 2.6. Remotely Administered Educational Session

The DHSG will receive a remote synchronous session of 1 h with guidance regarding familiarization with the use of the VSee platform. The Vsee platform is a secure, high-resolution videoconferencing software. It is easy to use, and it does not need to download any software system to the device. During this session, a verbal presentation will be carried out on how children and parents have to use the equipment to measure their heart rate, oxygen saturation, and how they should assess dyspnea and leg fatigue with the Dalhousie Pictorial Scale. Furthermore, parents/guardians will be trained on the proper use of the above equipment. Additionally, verbal instructions will be given to minimize difficulties relating to internet connection.

### 2.7. Assessment Procedure

All outcome measures will be assessed at the following time points: baseline (before the intervention), the end of the intervention (12 weeks), and follow-up (6 months after the intervention has ended). Assessment procedures will be performed in person at the hospital by a blinded, independent assessor (physiotherapist) on two consecutive days to avoid participant fatigue. Anthropometric characteristics, including weight, height (to calculate body mass index, BMI), fat mass (kg and %), and fat-free mass, will be measured using a stadiometer and the digital fat mass scale TANITA RD-545 (Tanita Corporation, Tokyo, Japan). Pulmonary function will be assessed through the performance of spirometry (Jaeger Vyntus Pneumo, Vyaire Medical, Mettawa, IL, USA) and the forced oscillation technique (FOT) (Jaeger Vyntus IOS, Vyaire Medical, Mettawa, IL, USA) [23,24]. Functional and exercise capacity will be assessed using the 6-minute walking test, the modified shuttle walk test, and the Chester step test. Respiratory muscle strength, handgrip, health-related quality of life (HRQoL), cough-specific QoL, physical activity (PA), and sedentary behavior will be assessed. Furthermore, twice a month for both groups, ACT performance and symptom behavior will be recorded in a detailed diary.

### 2.8. Outcome Measurement

#### 2.8.1. Primary Outcome

##### Exercise Capacity (Modified Shuttle Walk Test)

Maximal exercise capacity will be assessed through the modified shuttle walk test (MSWT). Its reliability has been previously evaluated in the pediatric population with CF [9]. In pediatric populations with CF, a 60 m improvement in the MSWT following a 6-week home-based exercise program has been identified as the minimal clinically important difference [25]. During the MSWT, participants will be asked to walk rapidly at gradually increasing speeds (15 levels total) along a 10 m corridor [26,27]. An audio signal (“beep”) will mark the transitions between levels, signaling a required increase in velocity. The protocol will commence at a baseline speed of 0.5 m/s (Level 1), with an incremental increase of 0.17 m/s for each subsequent level. The test will be terminated based on inability to continue, symptomatic fatigue, or the failure to reach the course marker before the auditory signal on two consecutive occasions. The walking distance (MSWD) will be recorded, and performance will be compared based on the equation proposed by Pinho et al. [28]. Two trials will be performed, with at least a 30 min rest. Before, during, and after (recovery period), cardiorespiratory parameters will be continuously recorded.

##### Compliance with the Airway Clearance Techniques and Exercise Program

Compliance with the ACTs will be recorded using a detailed diary that includes weekly symptoms, type, frequency, and duration of ACTs performed. For both groups, compliance will be assessed twice a month, following the completion of this diary. The DHSG will complete the diary through the website, while the CG will complete it in a paper version via a phone call from a physiotherapist. Furthermore, the DHSG’s exercise program compliance will be assessed every second online session through a Microsoft Form diary. Documentation of the percentage of completed synchronous videoconferencing sessions will also be performed.

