### 2.2. Randomization

To ensure blinding, an external individual who is not involved in the study will allocate participants randomly to each group using the randomizeR—R package, Version 1.4.2 (RWTH Aachen University, Aachen, Germany) (1:1 simple randomization), executed on an Apple macOS system [19], and will prepare the concealed opaque envelopes that will be given to the participants. Due to the nature of the study, the participants cannot be blinded. However, the study physiotherapist who will assess outcome measures, as well as the researcher who will perform the data analysis, will be blinded to participants’ group allocation.

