### 2.4. Eligibility Criteria

Eligible children will be screened based on a diagnosis of PCD, PBB, and NCFB, established via medical history, clinical features, or/and computed tomography and bronchoscopy findings. Inclusion criteria require children to be aged 6 to 12 years old, clinically stable with an absence of pulmonary exacerbation four weeks before the study’s recruitment, and maintain adherence to attending regular medical follow-up from a pediatric pulmonologist every three months. Regarding the diagnostic scope, children with cystic fibrosis will be excluded. Furthermore, children with immunodeficiency or asthma as their primary condition will also not be included. Additional exclusion criteria include children with clinical evidence of cardiovascular, neuromuscular, metastatic, or psychiatric comorbidities, and neuromuscular or musculoskeletal impairments that affect mobility and the ability to follow instructions. Ineligible children will also include those who have a medical history of lung transplants, who participate in other rehabilitation programs or attend regular physiotherapy ACT sessions (>10 sessions in a 3-month period), lack access to the internet (e.g., no smartphone, tablet, or laptop), or children and/or caregivers who are unable to use technological devices.

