**Primary outcomes**					
Exercise capacity (MSWT)			X	X	X
Compliance (ACTs and exercise)			X	X	X

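### ACT compliance is collected by a different mode in each arm, so a reporting or non-response difference between modes cannot be told apart from a treatment effect

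*Protocol article*

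**What the plan says.** Section 2.8.1 (Compliance with the Airway Clearance Techniques and Exercise Program) describes one diary for both arms: "Compliance with the ACTs will be recorded using a detailed diary that includes weekly symptoms, type, frequency, and duration of ACTs performed". The schedule is also common: "For both groups, compliance will be assessed twice a month, following the completion of this diary". The mode is not: "The DHSG will complete the diary through the website, while the CG will complete it in a paper version via a phone call". A physiotherapist makes that call.

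Other parts of the article bear on this:

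- **Outcome tier.** Compliance is placed under the primary outcome in 2.8.1 and in Table 1, and ACT compliance against usual care is part of the primary hypothesis in the Discussion. The abstract instead makes ACT adherence the secondary objective.
- **The website.** Under 2.5.1 the website is part of the intervention. The DHSG alone gets automated weekly reminders, can contact healthcare professionals through the site, and has two supervised video sessions a week.
- **Blinding.** Section 2.2 says that participants cannot be blinded, but that "the study physiotherapist who will assess outcome measures, as well as the researcher who will perform the data analysis, will be blinded" to allocation.
- **Eligibility.** Section 2.4 excludes children who "lack access to the internet (e.g., no smartphone, tablet, or laptop", and also children or caregivers who cannot use such devices.

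**The concern.** A between-arm comparison of a self-report is fair only if both arms report in the same way. Here one arm types entries into a site that belongs to its treatment, and the other completes a paper record through a conversation with a physiotherapist. These modes can differ in how readily families overstate what they did, how complete the record is, and how often no record arrives.

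Each mode occurs in one arm only, so any such difference is added to the estimated effect on compliance. What is at stake is the compliance half of the primary hypothesis. A positive result could reflect the mode, and a null result could conceal a real gain. Multiple imputation (section 2.10) does not repair this: it fills in missing entries but does not correct entries that are misreported.

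**Working it through.** **1. Is mode fully aligned with arm?**

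| | DHSG | CG |
|---|---|---|
| Diary content | symptoms; ACT type, frequency, duration | same |
| Frequency | twice a month | twice a month |
| Medium | intervention website | paper version |
| Human contact at collection | none stated | physiotherapist phone call |

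Content and timing match. Medium and contact differ, and no family in either arm is described as using the other arm's mode. The article describes no objective check of ACT performance common to both arms. The percentage of completed synchronous sessions exists only in the DHSG.

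**2. What the comparison estimates.**

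Observed difference = true difference + (reporting error in DHSG − reporting error in CG).

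The bracket is zero only if both modes err equally. The article gives no compliance rates or error sizes, so the following are assumptions. Take true compliance of 60% in the DHSG and 45% in the CG, a true difference of 15 percentage points.

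| Over-report (points) | If in CG only | If in DHSG only |
|---|---|---|
| 5 | 15 − 5 = 10 | 15 + 5 = 20 |
| 10 | 15 − 10 = 5 | 15 + 10 = 25 |
| 15 | 15 − 15 = 0 | 15 + 15 = 30 |

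The same design fault can erase the effect or double it.

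**3. The plan's own figure.** The article gives no sample size for compliance. Its sample size in 2.9 is set on exercise capacity: f = 0.25, alpha 0.05, power 80%, two groups. With the three time points of 2.10, and assuming a correlation of 0.5 and no sphericity correction (neither is stated), the noncentrality is f² × N × m/(1 − rho) = 0.0625 × 28 × 3/0.5 = 10.5. Power is 0.812 at N = 28 and 0.778 at N = 26. Then 28/0.9 = 31.1, which becomes 32 with equal arms. The figure reproduces. It is used here only for the arm sizes: 16 randomised per arm, or 14 after dropout.

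**4. False-positive rate from mode alone.** Assume no true difference in compliance, a constant reporting shift of b standard deviations between modes, and a two-sided t-test at 0.05. The noncentrality is b × √(n/2) with 2n − 2 degrees of freedom. For example, n = 16 and b = 0.50 give 0.50 × √8 = 1.41.

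| Shift b (SD) | 14 per arm | 16 per arm |
|---|---|---|
| 0 | 5.0% | 5.0% |
| 0.10 | 5.7% | 5.9% |
| 0.25 | 9.8% | 10.5% |
| 0.50 | 24.7% | 27.8% |
| 0.75 | 48.0% | 53.7% |
| 1.00 | 72.1% | 78.1% |

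The error rate rises with n, so more children would not help. This is a single between-arm comparison, simpler than the planned 2 × 3 ANOVA, and shows only how the result depends on b.

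**The case against.** **The difference is smaller than it looks.** Content and frequency are the same, and the control record is nominally a paper diary completed via the call, not a bare interview. If the paper is filled in as the days pass and merely read out, recall and interviewer effects shrink. This stands as mitigation, but the two modes still differ.

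**Change from baseline could cancel the shift.** Table 1 marks compliance at baseline, after allocation, and the planned test is a group × time interaction. A mode effect that was constant over time would drop out if baseline were collected in the same arm-specific way. The article does not say how baseline compliance is collected. Nor is constancy plausible if entries depend on engagement with the website.

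**Three stronger readings are tempting, and the article does not support them.**

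- *The bias runs against the intervention*, because the call inflates and prompts control reports while web entries go missing. The opposite is equally arguable: DHSG families are unblinded, see the team twice a week, enter data on its website and receive weekly reminders, so they may over-report. A call that makes controls do more ACT would also be a real change in behaviour, not a reporting error.
- *Missingness will differ by arm.* It may, since a family that drops the website may also drop the diary. Nothing in the article establishes it.
- *The blinding statement in 2.2 is contradicted.* Only CG families are phoned for the routine diary, so the caller can infer the arm. But 2.7 describes the blinded assessor as working in person at the hospital, and 2.8.1 does not say that the caller is that person. Blinding for the diary is unspecified rather than contradicted.

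**Conclusion.** The concern holds for the difference in mode: as written, mode and arm coincide for ACT compliance, and the diary data cannot separate a mode effect from a treatment effect without an untestable assumption. Confidence in that is high. The size and direction of the bias are unknown. The percentages above rest on assumed shifts and show only that a moderate shift would matter, since 0.50 SD takes a nominal 5% error rate to about 25–28%.

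The scope is limited to ACT compliance compared between arms. That is a primary outcome by 2.8.1 and Table 1 and a secondary objective by the abstract, and on either label it is a main claim of the trial. The modified shuttle walk test is measured in person in both arms and is unaffected. Exercise-program compliance is recorded only in the DHSG, so no between-arm comparison of it arises. The change should be made before recruitment starts, because analysis cannot recover it afterwards.

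**What to change.** Collect the ACT diary in both arms with the same stand-alone online form, kept off the intervention website, on the same twice-monthly dates and with the same diary reminder. Microsoft Forms is already used in the trial for the exercise diary. For families who do not respond, use the same scripted fallback call in both arms, made by someone who does not deliver the intervention and who is, where possible, unaware of allocation. Collect any baseline compliance measure in the same way.

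The cost is one extra form link and a short call script, offset by dropping the routine control calls. The eligibility rules on internet access and device use mean that control families can complete the form without being given the intervention site. There are small downsides: some control families may answer a form less readily than a call, and DHSG families will use a form separate from the website they already visit.

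The DHSG's weekly ACT reminders can stay, as they are part of the intervention. The change makes measurement the same in both arms. It does not turn a self-report by unblinded families into a blinded outcome, and the report should say so.
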